### Data collection

There are three data collection points for both intervention and control groups: recruitment (T_1_), 3 months postrandomization (T_2_), after 8 months of pregnancy (T_3_), and 3 months postpartum (T_4_)_._ (Fig. 1). All questionnaires will be completed online though a web application. Participants will receive computer-generated emails or smartphone reminders to complete questionnaires. These reminders will occur at 1, 3, and 7 weeks.

In addition to the online questionnaires and online modules, participants in the intervention group will be asked to participate in interviews regarding the feasibility and acceptability of the intervention. Additionally, women will be asked about suggestions for improving the e-IPT. Thirty women in the intervention group will complete the interviews. Using a semistructured interview schedule, these women will be asked about their experiences with the online intervention. These interviews will be transcribed verbatim and then coded and analyzed using an inductive thematic analysis approach [76].

### Data analyses

#### Feasibility and acceptability of the intervention

Feasibility and acceptability, in addition to the qualitative data obtained from the interviews, will be characterized using descriptive statistics (frequencies, proportions, means, standard deviations). Feasibility will be assessed as the rate of retention in the study and percentage of modules completed. The acceptability of this intervention will consist of an analysis of the perceptions of the prenatal women regarding the intervention and its various features. Acceptability will be assessed by open-ended questions exploring the reported ease for women in navigating the online intervention. Participants will also be asked about what was useful and that was difficult in navigating this online intervention. The qualitative data will be analyzed using inductive thematic analysis. This method was chosen because it allows patterns and key themes within the data to be identified [76]. The three-stage process of thematic analysis will involve: 1) generating code; 2) merging and renaming similar codes; and 3) grouping codes into overarching themes that best describe the data [77].

#### Quantitative analysis

The quantitative dataset will be analyzed using IBM SPSS Statistics software. Missing values will be managed by using multiple imputation [78]. Assessment of the presence of any outliers will be made, and it will be determined if they are true values or data entry errors [78]. If not determined as an entry error, the analysis will be run with the outliers included and then run without the outliers included. Results will be compared and whether the outliers skew the results and what it means on a clinical level will be reported. If the results do not differ, then the analysis with the outliers included will be used. Outcomes will be assessed based on the number of modules completed. Additionally, a sensitivity analysis will be completed by running a negative binomial regression model which accounts for variance in the data. Descriptive statistics (mean/standard deviation or frequency/proportions) will serve to describe the characteristics of participants and assess group equivalence at baseline. Repeated measures analysis of variance will be used to determine the effectiveness of the intervention. The variables will be included in the analysis as covariates and bivariate analysis will be performed first. Those variables found to be statistically significant at the bivariate level will be included in the multivariate model. Analysis will adhere to the intent-to-treat principle [78].

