### Research objectives, questions, and hypotheses

The primary aim of this pilot randomized controlled trial is to examine feasibility and acceptibility of e-IPT for prenatal women. The assessment of feasibility will include the percentage of women in the intervention group who report that the e-IPT is integrated as a component of prenatal care without difficulty. Acceptability will be assessed in terms of the percentage of women in the intervention group who report that modules and activities in e-IPT are easily understood and navigated. The primary research objective, question, and hypothesis are described in Table 1. The secondary objectives include assessment of symptoms of anxiety, depression, overall psychological distress, relationship quality (spouse, immediate family members), and mother resilience compared to routine care. We hypothesize that the e-IPT intervention will reduce symptoms of distress, anxiety and depression and will be significanly more effective compared to usual care. These secondary research objectives, questions, and hypotheses are described in Table 2.

**Table 1 Tab1:** Primary objective, research questions, and hypothesis

	Objective	Research questions	Testable hypothesis
1	To assess the feasibility and acceptability of online interpersonal psychotherapy for prenatal women	Do prenatal women find the online IPT intervention is easily integrated as a component of prenatal care without difficulty? Do prenatal women find the online IPT intervention acceptable? What will improve the performance of online interpersonal psychotherapy in a full trial version for prenatal women? Is it feasible to enroll and retain prenatal women in a study to assess an online IPT intervention? Is it feasible to perform data collection procedures as planned? Is it feasible to deliver the IPT program as intended?	Prenatal women will define strategies to enhance online interpersonal psychotherapy, readying it for a full trial

*IPT* interpersonal psychotherapy

**Table 2 Tab2:** Secondary objectives, research questions, and hypotheses

	Objective	Research question	Testable hypotheses

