1	To evaluate the clinical effectiveness of online interpersonal psychotherapy versus routine care on reducing stress, anxiety, and depression in prenatal women	What is the effect of an online interpersonal psychotherapy intervention compared to routine care on the percentage of prenatal women with symptoms of stress, anxiety, and depression?	The percentage of prenatal women with stress, anxiety and depression about the clinical cut-offs of validated tools will be significantly lower in the intervention group versus routine care
2	To evaluate the effectiveness of the online interpersonal psychotherapy intervention compared to routine prenatal care on relationship distress	Is relationship distress reduced in the online interpersonal psychotherapy intervention group compared to the routine prenatal care control group?	Relationship distress will be significantly reduced in the online interpersonal psychotherapy group
3	To identify factors, mediators and moderators that are associated with effectiveness of the intervention among participants within the intervention group	What factors, mediators, and moderators are associated with the intervention effect?	Among participants in the intervention group, no factors will be significantly associated with the intervention effect, indicating that online interpersonal psychotherapy is appropriate for prenatal women

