### Sample size estimation

The DASS21 categorizes women as having normal, mild, moderate, severe, and extremely severe depression, anxiety and stress [56]. To shift women from ‘midrange’ moderate symptoms down to mild severity on the depression, anxiety and stress subscales, these women would require a reduction of four points in each subscale. Based on the sample size formula for comparison of two means (two-tailed) at a significance level of 5% (1.96), a power of 80% (0.84), and a minimally clinically important difference of four points, 204 women with mild to moderate psychological distress are required in the trial. Based on a 25% prevalence rate of low–moderate prenatal psychological distress [69–71], a final sample size of 816 eligible women (408 per group) would be needed. This corresponds to a moderate effect size (*d* = 0.50) for depression, which is consistent with a meta-analysis of effect sizes of e-IPT [25]. Therefore, this final sample size of 816 participants is adequate to address the primary and secondary research questions of a full trial. Accounting for a participation rate of 50% based on previous studies of psychotherapy in pregnant women [55, 72, 73], the exclusion of 15% of women who do not meet study criteria (5% high psychosocial risk [70, 71, 74], 10% non-English speaking women), an attrition rate of 25% based on previous studies of perinatal IPT [20, 55], and a 5% loss to follow-up, 1592 women would need to be invited to participate in the study to achieve the final full trial sample size. As this is a pilot study, obtaining a sample size of 10% of the full trial sample is sufficient [75]; therefore 160 participants will be included in the pilot study with 80 participants in the intervention and control groups, respectively.

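### Table 2 hypothesises about percentages above cut-offs and the sizing uses a mean difference in distressed women, but the analysis compares mean scores without restriction to those women, so the full-trial adequacy statement does not carry over

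*Protocol article*

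**What the plan says.** Four parts of the protocol article bear on this.

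- **Hypothesis.** Table 2, secondary objective 1: "The percentage of prenatal women with stress, anxiety and depression about the clinical cut-offs of validated tools will be significantly lower" in the intervention group than under routine care. I read the third-to-last noun phrase as meaning above the cut-offs. The outcome is binary. The text of the same section words the aim differently: "We hypothesize that the e-IPT intervention will reduce symptoms of distress, anxiety and depression", and adds that e-IPT will be significantly more effective than usual care.
- **Sizing.** Sample size estimation uses a two-means formula, two-sided 5%, 80% power, with "a minimally clinically important difference of four points, 204 women with mild to moderate psychological distress are required in the trial". It divides 204 by a 25% prevalence to reach 816 (408 per group), says this corresponds to "a moderate effect size (*d* = 0.50) for depression", and calls 816 adequate for the primary and secondary questions of a full trial. The pilot's 160 (80 per group) is justified as a fraction of the full trial, with no power claim.
- **Who enters.** Inclusion and exclusion criteria set no distress threshold.
- **Test.** Quantitative analysis: "Repeated measures analysis of variance will be used to determine the effectiveness of the intervention". The analysis follows intent-to-treat. The only other outcome model named is a negative binomial regression, as a sensitivity analysis. Frequencies and proportions appear only for describing participants and baseline balance.

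**The concern.** Hypothesis, sizing and test differ in two ways that matter.

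**Scale.** The Table 2 hypothesis concerns a proportion. Neither repeated-measures ANOVA nor negative binomial regression is a model for a proportion, so the plan names no analysis for that hypothesis.

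**Population.** The sizing counts only the distressed quarter of recruits. The analysis, as far as the article describes it, includes everyone. If benefit is concentrated in the distressed quarter, the average difference is diluted while the adequacy statement stays the same.

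The Abstract says the pilot will inform the evaluation strategy and the sample size calculations of the full trial, so an unresolved contrast would be carried forward. In the pilot itself, hypotheses worded as significant differences are set for 160 women without any power to support them.

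**Working it through.** **Inputs from Sample size estimation:** two-sided 5% (1.96), power 80% (0.84), difference 4 points, 204 distressed women, 25% prevalence, 408 per group, d = 0.50 for depression, pilot 80 per group, attrition 25%, loss to follow-up 5%. **Not given:** the SD, the percentages above cut-off, the correlation between visits. These are assumptions below.

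**1. The plan's own figure.** n per arm = 2(1.96 + 0.84)² SD² / 4².
- d = 0.50 with 4 points implies SD 8: 2 × 7.84 × 64 / 16 = 62.7, so 63 per arm, 126 in all. The plan states 204.
- Solving back from 204 (102 per arm): SD = 4 × √(102 / (2 × 7.84)) = 10.2, d = 0.39.
- 204 / 0.25 = 816 reproduces.

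I do not call 204 wrong: no SD is stated, and d = 0.50 is given for depression only, so another subscale may have set it. I carry SD 8 to 10.2 as the range. Within the distressed group, 102 per arm gives 80% power at SD 10.2 and about 95% at SD 8.

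**2. Mean difference in all women, full trial.** Extreme case: 4 points in the distressed 25%, none in the rest. Average = 0.25 × 4 = 1 point. Noncentrality at one time point = (1/SD) × √(408/2).
- SD 8: 1.79, power 43%.
- SD 10.2: 1.40, power 29%.
- SD 6 to 12: 66% down to 22%.

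**3. Four-time-point ANOVA, 408 per arm, correlation 0.5, no effect at T1.** The article does not say which term is tested, so both are shown.
- Group term: difference 0.75 × 1 = 0.75; SD of a woman's mean = SD × √((1 + 3 × 0.5)/4), i.e. 6.32 or 8.06. Power 39% or 26%.
- Group-by-time term (3 df): noncentrality = 204 × (0.75² + 3 × 0.25²) / (SD² × 0.5) = 4.78 or 2.94. Power 42% or 27%.

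**4. A more efficient analysis that the article does not specify.** Baseline-adjusted mean of three follow-ups, SD multiplied by √((1 + 2ρ)/3 − ρ²), ρ from 0.3 to 0.7: 77-89% at SD 8, 56-71% at SD 10.2.

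**5. Percentage above cut-off, 408 per arm, assumed control rate 25%.**

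| Intervention rate | Power, 408/arm | Power, 80/arm |
|---|---|---|
| 20% | 40% | 11% |
| 17.5% | 75% | 21% |
| 15% | 95% | 35% |

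The power depends wholly on rates that the article does not give.

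**6. Pilot.** For the 1-point average at one time point: 9-12% with 80 per arm, and 8-10% with 80 × 0.75 × 0.95 = 57 per arm. The ANOVA terms in step 3 give 9-12% at 80 per arm. In the distressed women only (160 × 0.25 = 40, or 20 per arm), a 4-point effect has about 23-35% power, and 17-25% after the stated attrition and loss (40 × 0.75 × 0.95 = 28.5 women).

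**The case against.** **The 80% is not claimed for this analysis.** It is stated for a hypothetical 816-woman trial; the ANOVA is described for the 160-woman pilot, where effectiveness is secondary. A reader might infer that the plan promises 80% power for the pilot's ANOVA. It does not. This stands, and it moves the fault to the adequacy sentence and the significance wording.

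**The text also speaks of reduced symptoms.** A comparison of means does address that wording, so it would be too strong to say that effectiveness is never tested. What remains is that the text and Table 2 differ, and that the Table 2 form has no named analysis.

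**Two-means sizing followed by repeated measures is not a fault.** Both compare means. A reader might also conclude that the ANOVA is diluted by treating T1 as an outcome level. The article does not say that the group main effect is the test, and such detail is commonly left to an analysis plan. This stands.

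**The size rests on assumptions.** Zero effect in the other 75% is extreme. The 25% is low-moderate distress and the eligibility section does not exclude severely distressed women, so some of the rest have room to improve. With baseline adjustment and three follow-ups the loss is much smaller (step 4). This also stands: the figures show sensitivity and are not a forecast. It does not restore the adequacy claim, because nothing in the article ties the 80% to either contrast.

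**Conclusion.** The concern holds in a limited form. Table 2 sets a hypothesis about percentages for which the article names no analysis, and 816 is called adequate for the full trial's questions although its 80% power belongs only to a mean comparison within distressed women.

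Under SD 8 to 10.2 and no effect in the other 75%, power in all 816 women is about 29-43% at one unadjusted time point and about 26-42% for the four-time-point ANOVA at correlation 0.5. It is higher if the effect extends beyond the distressed quarter or if follow-ups are combined and adjusted for baseline. For the percentages it was 40-95% across the rates tried. In the pilot the 1-point average has about 8-12% power.

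A reader might go further and say that the pilot is bound to give a null result that will be misread as ineffectiveness. The documents do not support that: power is that low only in the extreme case, and the Abstract presents the pilot as informing feasibility, adaptation and sample size. Because effectiveness is secondary here, this should be corrected but does not undermine the pilot's primary aim.

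**What to change.** 1. Analyse the percentage above named DASS21 and EPDS cut-offs with a logistic model adjusted for the pre-randomisation score.
2. Analyse mean scores in all randomised women, adjusted for the pre-randomisation DASS21 or EPDS score. Prespecify the women with mild to moderate distress at that screen as the subgroup that matches the sizing. Making this subgroup the leading analysis would be a trade-off (about 20 women per arm, severely distressed women left out) and is not needed.
3. In the pilot, report estimates with 95% confidence intervals, and replace the significance wording in Table 2 and in the accompanying text with estimation wording.
4. In Sample size estimation, say that 80% power applies only to a comparison of means within the distressed subgroup of a full trial, and state the SD used.

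The cost is wording and analysis code. DASS21 and EPDS are already collected before randomisation, so no new data are needed. The small downside is that the pilot gives up significance claims it could not support, and the stated adequacy becomes less favourable.

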### Both groups

All applicants will complete the Depression, Anxiety, and Stress Scale-21 (DASS21) and the Edinburgh Postnatal Depression Scale (EPDS) on recruitment (prerandomization) to provide baseline data on their mental health status. All participants (control and intervention groups) assessed as having thoughts of self-harm will receive a computerized message offering then crisis line/emergency room contact information and informing them that they will be contacted by the study nurse. Following randomization, participants will complete the baseline series of questionnaires which comprehensively assess a variety of demographics and psychosocial constructs (T_1_) (Fig. 1). These questionnaires will be completed again at 3 months postrandomization (T_2_), after 8 months of pregnancy (T_3_), and 3 months postpartum (T_4_).

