### Methods to protect against bias: randomization and blinding

Eligible women will complete the consent to participate in the online app and will then be automatically randomized within the app at a 1:1 control to treatment ratio. Immediately following randomization women will be notified of their group assignment through the app. Participants are not blind to their group allocation, nor are their health-care providers who are informed of the screening results of their patients (if the participant consents to fax a report to her health-care provider) and recommendation for e-IPT.

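### Effectiveness is tested by classical repeated measures ANOVA on multiply imputed data with no contrast named to pool, so the stated methods do not lead to one combined test or to a group difference with a confidence interval

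*Protocol article*

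**What the plan says.** The Quantitative analysis section fixes three things that bear on this point:

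- Software: "The quantitative dataset will be analyzed using IBM SPSS Statistics software".
- Missing data: "Missing values will be managed by using multiple imputation [78".
- Test of effectiveness: "Repeated measures analysis of variance will be used to determine the effectiveness of the intervention".

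The section also commits to intention to treat. It does not name the ANOVA term that carries the effectiveness question, a contrast or estimate to report, or a way of combining results across imputed datasets.

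The Both groups section sets a baseline and three follow-ups: "These questionnaires will be completed again at 3 months postrandomization (T_2_), after 8 months of pregnancy (T_3_), and 3 months postpartum (T_4". For missing data, the only planning figures are in Sample size estimation: "an attrition rate of 25% based on previous studies of perinatal IPT [20, 55], and a 5% loss to follow-up".

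Effectiveness is a secondary aim. The primary outcome is feasibility and acceptability, which is summarised descriptively and by thematic analysis.

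**The concern.** The ANOVA uses only women with a score at every visit. Under intention to treat, every woman who misses a visit therefore enters through imputed scores. Multiple imputation returns one ANOVA table per completed dataset. Rubin's rules in their usual scalar form combine an estimate and its standard error, and an F ratio is neither. With no contrast named, the step from several ANOVA tables to one result is undefined. The shortcuts closest to hand are averaging the F ratios, averaging the p values, or reporting a single imputed dataset. None of these carries the between-imputation variance properly.

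Two uses of the results are at stake. The objectives section expects e-IPT to be significantly more effective than usual care, so these p values will be read. The abstract also says that the pilot will inform the sample size of the full trial. That needs a group difference with a valid confidence interval, which an F ratio does not give.

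**Working it through.** **Inputs from the protocol article**

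- Pilot size: "160 participants will be included in the pilot study with 80 participants in the intervention and control groups, respectively".
- Allocation: "automatically randomized within the app at a 1:1 control to treatment ratio".
- Visits: four (T1 to T4).
- Level: 5% two-sided. It is stated only for the sample size formula ("comparison of two means (two-tailed) at a significance level of 5% (1.96") and is carried over here.
- Missing data: 25% attrition and 5% loss. Added, this is 30%. Applied in sequence, it is 1 − 0.75 × 0.95 = 28.75%. On 160 women, 25–30% missing is 40 to 48 women without a complete record.

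**Assumptions not in the protocol article**

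Normal scores; T1 complete; monotone dropout completely at random; compound symmetry with correlation 0.3–0.7 (AR(1) with 0.7 as a check); m = 5 or 20 imputations from a proper sequential regression model that includes group.

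**Tests compared**

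The protocol article gives no false-positive figure to reproduce, and no closed formula applies, so the rates come from simulation under no effect.

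1. Averaged F: the mean of the m group-by-time F ratios, referred to F with 4 − 1 = 3 and (160 − 2) × 3 = 474 degrees of freedom.
2. Averaged p: the mean of the m p values, compared with 0.05.
3. D1, the multi-parameter extension of Rubin's rules, on the k = 3 group-by-time contrasts. With q̄ the mean contrast vector, Ū the mean within-imputation covariance and B the between-imputation covariance:
 r = (1 + 1/m) tr(B Ū⁻¹)/k
 D1 = q̄ᵀ Ū⁻¹ q̄ / [k(1 + r)]
 For a single contrast, the scalar rule gives total variance Ū + (1 + 1/m)B.

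**Results, group-by-time rejection rate**

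Compound symmetry; 3000 runs for m = 5 and 1500 for m = 20. Ranges at m = 5 are over correlations 0.3, 0.5 and 0.7; m = 20 was run at 0.5.

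| Missingness | m | Averaged F | Averaged p | D1 |
|---|---|---|---|---|
| Rising to 25% at T4 | 5 | 11.0–12.3% | 7.8–8.5% | 5.5–5.8% |
| Rising to 29–30% at T4 | 5 | 12.3–13.2% | 8.0–9.1% | 5.2–5.8% |
| 25% at every follow-up | 5 | 13.9–16.3% | 9.0–9.5% | 4.8–5.2% |
| 30% at every follow-up | 5 | 18.2–20.5% | 10.9–12.3% | 4.6–5.6% |
| Rising to 25% at T4 | 20 | 10.2% | 6.1% | 4.8% |
| Rising to 30% at T4 | 20 | 12.7% | 7.9% | 6.1% |
| 30% at every follow-up | 20 | 20.1% | 9.5% | 6.3% |

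Checks:

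- In the m = 5 rows, the ANOVA on full data rejects in 4.0–5.4% and on complete cases in 4.2–5.5%. The excess therefore arises when the imputed tables are combined.
- A Greenhouse–Geisser correction moves the averaged-F rates by less than 1 point under compound symmetry. Under AR(1) the corrected rates are 9.3–14.4%, and averaged p gives 7.5–10.3%.
- Monte Carlo standard error with 3000 runs: √(0.05 × 0.95/3000) = 0.4 points at 5% and √(0.20 × 0.80/3000) = 0.7 points at 20%. With 1500 runs: 0.6 and 1.0 points.

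**Second simulation** (correlation 0.5, 15/25/30% missing at T2/T3/T4, m = 20, 1500 runs)

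- Group by time: 14.7% for averaged F, 16.6% from one imputed dataset.
- Group main effect: 6.0% and 6.3% respectively.
- Group contrast at T4: 12.5% from one imputed dataset, 4.5% when pooled by Rubin's rules.

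**The case against.** The strongest reply is that the plan commits no such error. It never says that F or p values will be averaged or that one dataset will be used. The pooling rule, the imputation model and the number of imputations normally belong in an analysis plan, which is not shown. That is right, and their absence is not the point here. The point is the test that the article does name: a classical ANOVA yields F ratios rather than an estimate to pool, and a better-suited model is available.

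A reader might infer that multiple imputation with ANOVA admits no valid p value. The documents do not support that. The group-by-time hypothesis is a set of mean contrasts, which can be estimated in each dataset and pooled; D1 then rejects in 4.6–6.3% under compound symmetry.

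A reader might also infer a bias towards e-IPT. The group-by-time F has no direction, so under no effect with equal dropout the false positives fall either way.

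Two further limits stand. The 25% and 5% are used to inflate recruitment for the full trial, not as a visit-by-visit forecast for the pilot. Nor is the analysis mostly imputed: with 0/15/25/30% missing, (0 + 15 + 25 + 30)/4 = 17.5% of scores are filled in.

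**Conclusion.** The concern holds in a limited form. The stated test and the stated missing-data method do not by themselves lead to one combined test or to a group difference with a confidence interval, because the F ratios cannot be pooled by the scalar rules and no contrast is named.

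The size is conditional. If F ratios were averaged, the group-by-time false-positive rate would be roughly 10–20% at 25–30% missing. Gradual dropout gives about 10–13%, and the same loss at every follow-up about 14–20%. Averaged p values would give 7.5–12% with five imputations and 6.1–9.5% with twenty. The main effect would stay near 6%. These figures rest on the assumed correlation, dropout pattern, normality, data missing completely at random and number of imputations.

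It would be tempting to report a single inflated error rate as a property of this trial. The document does not support that, since the averaging step is hypothetical and the inputs that set the rate are not fixed. The primary feasibility and acceptability results are unaffected. What is affected is the secondary effectiveness comparison and its use in planning the full trial.

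**What to change.** In the Quantitative analysis section, replace the repeated measures ANOVA with a linear mixed model for repeated measures, with visit, group and group by visit as effects and an unstructured within-woman covariance, fitted to all observed scores. Report the group difference at each visit with its 95% CI. This uses partial records without requiring a score at every visit and gives the estimate that full-trial planning needs. The mixed model was not itself simulated here; the recommendation rests on its general properties.

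If multiple imputation is kept, estimate the same contrasts in each imputed dataset and pool estimates and standard errors by Rubin's rules, with D1 for the joint group-by-time test. State that F and p values will not be averaged.

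The cost is wording in the analysis section. No new data, visits or participants are needed.

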**Methods:**

A pilot randomized controlled trial design with repeated measures will evaluate the feasibility and acceptability of e-IPT for pregnant women compared to routine prenatal care. Qualitative interviews with 15–30 individuals in the intervention group will provide further data on the feasibility and acceptability of the intervention. Assessment of feasibility will include the ease of accessing and completing the intervention. Women will also be asked about what barriers there were to starting and completing the e-IPT. Assessment of acceptability will inquire about the perception of women regarding the intervention and its various features. A sample size of 160 consenting pregnant women aged 18 years and older will be enrolled and randomized into the experimental (e-IPT) or control (routine care) condition. The secondary outcome measures include: depression, anxiety and stress symptoms; self-efficacy; self-mastery; self-esteem; relationship quality (spouse, immediate family members); coping; and resilience. All participants will complete the aforementioned measures at baseline during pregnancy (T_1_), 3 months postrandomization (T_2_), at 8 months of pregnancy (T_3_), and 3 months postpartum (T_4_).

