##### Variables

Variables that are associated with (and may mediate) the effectiveness of the e-IPT will be explored through an examination of variables that may be influential in the perinatal mental health theories and literature. The factors to be included were selected based on their association with perinatal depression, anxiety and stress. As a result, the influence of self-efficacy, social support, sense of mastery, self-esteem, sleep, coping, and resilience will be explored. Additionally, the association of preconception of mental health problems such as borderline personality disorder, perfectionism, and attention deficit/hyperactivity disorder will be investigated. These variables will be included as covariates in the data analysis models.

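### The effectiveness analysis admits possible mediators as covariates by bivariate significance and does not restrict them to pre-treatment values

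*Protocol article*

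**What the plan says.** Under Secondary outcomes, the Variables section opens with "Variables that are associated with (and may mediate) the effectiveness of the e-IPT will be explored". It then says that "the influence of self-efficacy, social support, sense of mastery, self-esteem, sleep, coping, and resilience will be explored", adds that "preconception of mental health problems such as borderline personality disorder, perfectionism, and attention deficit/hyperactivity disorder will be investigated", and closes with "These variables will be included as covariates in the data analysis models".

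The Quantitative analysis section names the effectiveness model: "Repeated measures analysis of variance will be used to determine the effectiveness of the intervention". The next sentence enters the variables as covariates after a bivariate step, and the rule follows: "Those variables found to be statistically significant at the bivariate level will be included in the multivariate model". The section ends with a commitment to intention-to-treat.

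The abstract (Methods) gives the secondary outcomes as "depression, anxiety and stress symptoms; self-efficacy; self-mastery; self-esteem; relationship quality (spouse, immediate family members); coping; and resilience".

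On timing, the first Both groups section (before the randomisation section) has DASS21 and EPDS completed before randomisation and the T1 questionnaire series after it, with repeats at T2, T3 and T4. The section on randomization and blinding says that women learn their group at once. The Data collection section labels T1 as recruitment.

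**The concern.** The same variables hold three roles: possible mediator, outcome and adjustment covariate. Self-efficacy, mastery, self-esteem, coping and resilience hold all three. Social support and sleep are possible mediators and covariates but are not in the abstract's outcome list. Social support matters most here, because the section on the aim of IPT describes improving it as the purpose of the therapy.

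Conditioning on a variable that treatment has changed takes that pathway out of the treatment contrast. What remains is a direct effect, not the total effect of offering e-IPT. A significance screen adds to the problem: a strong mediator is strongly related to the outcome and so is likely to pass. Whatever values are used, the screen also leaves the covariate set unknown until the data are in.

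At stake are the secondary hypothesis that e-IPT outperforms usual care and, because the abstract's Discussion says the pilot will inform the full trial's sample size, any effect estimate carried forward.

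**Working it through.** **Roles of the candidate covariates**

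| Variable | Possible mediator (Variables) | Secondary outcome (abstract) | Candidate covariate |
|---|---|---|---|
| Self-efficacy, mastery, self-esteem, coping, resilience | yes | yes | yes |
| Social support, sleep | yes | no | yes |
| Borderline personality disorder, perfectionism, ADHD | no (pre-existing) | no | yes |

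**Which values may enter.** Neither section gives a time point. The questionnaires are repeated at T2 to T4, so post-treatment values will exist, and nothing excludes them.

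**Size if they enter.** The plan states no figure on this point to reproduce. The check was a simulation of 2,000 runs per setting, simplified to one candidate covariate and one follow-up.

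Inputs from Sample size estimation:
- 160 women, 80 per arm
- effect size 0.50
- two-sided 5% level

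Assumptions not in the documents:
- treatment shifts the mediator by 0.5 SD
- the mediator's baseline-to-follow-up correlation is 0.5
- the mediated share s is 0, 25, 50 or 75%
- the screen keeps a covariate whose correlation with the outcome has p < 0.05

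Model, with t = 1 for e-IPT, M0 the baseline and M1 the follow-up mediator:
- M1 = 0.5·M0 + 0.5·t + error
- Y = (1 − s)(−0.50)·t + b·M1 + error, with b = s(−0.50)/0.5 = −s

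The total effect is (1 − s)(−0.50) + (−s)(0.5) = −0.50 for every s. Given M1, the coefficient of t is (1 − s)(−0.50), which is −0.50, −0.375, −0.25 and −0.125 for the four shares.

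| Share mediated | No covariate: estimate (power) | Baseline value, screened | Post-treatment value, screened | Post-treatment value admitted |
|---|---|---|---|---|
| 0% | −0.498 (0.88) | −0.498 (0.88) | −0.491 (0.87) | 11% |
| 25% | −0.506 (0.88) | −0.504 (0.88) | −0.381 (0.66) | 97% |
| 50% | −0.504 (0.89) | −0.500 (0.90) | −0.251 (0.44) | 100% |
| 75% | −0.503 (0.88) | −0.501 (0.92) | −0.124 (0.20) | 100% |

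The Monte Carlo standard error of a power is at most √(0.25/2000) = 0.011. The simulated estimates match the algebra. Baseline values unaffected by allocation cost nothing and may add precision. Post-treatment values remove almost exactly the mediated share, and the screen admits them almost every time once 25% or more is mediated.

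**The screen itself.** It makes the covariate set a function of the outcome data, while the usual p-values and intervals treat that set as fixed. The size of this distortion was not computed.

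**The case against.** Several points on the other side stand.

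- **Time point.** A standard repeated measures ANOVA takes one covariate value per woman, and that may well be T1. The Background also describes predictors and moderators as pretreatment variables. A reader might infer that the model certainly removes part of the effect, or half of it. The documents do not support that: attenuation needs values from T2 to T4, and no mediated share is given.
- **T1 after disclosure.** A reader might infer that even T1 is contaminated because women already know their group. Two sections do place it there, but Data collection calls T1 recruitment. On either account T1 is described as the baseline series, so little effect of e-IPT on it is to be expected. The text neither shows an effect of knowing one's group nor rules one out.
- **Purpose of the screen.** The multivariate model is not expressly called the repeated measures ANOVA, and it could serve Objective 3 in Table 2, which looks for mediators and moderators. The sentence order and the closing line of the Variables section favour the effectiveness reading, but the text is not conclusive.
- **Intention-to-treat.** A reader might infer that this promise is broken. Baseline adjustment does not breach it; adjustment for post-treatment mediators would undercut it.
- **Weight.** The primary feasibility and acceptability outcomes are descriptive, and the stated full-trial size rests on a four-point difference, not on this estimate.

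None of this rescues the screen, which is a written rule and not a detail left for later. No unadjusted or fixed-covariate main analysis is named as a safeguard.

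**Conclusion.** The point holds in conditional form. The plan makes seven possible mediators, five of them also secondary outcomes, candidate covariates in the effectiveness analysis, selects them by bivariate significance and does not confine them to pre-treatment values.

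If later values enter, a true 0.50 SD effect at 80 per arm would be estimated at about 0.38, 0.25 or 0.12 SD for mediated shares of 25, 50 or 75%, with power falling from about 0.88 to 0.66, 0.44 or 0.20. These figures rest on the assumed shares, the assumed mediator shift and correlation, and a single-covariate, single-follow-up simplification. If T1 values are used, attenuation is little or none. On both readings the covariate set is data-driven, so nominal p-values and intervals are not assured.

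This is a should-fix for the secondary effectiveness analysis. It does not touch the primary outcomes.

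**What to change.** 1. In Quantitative analysis, delete the bivariate screen. Estimate the treatment effect with a covariate set fixed in advance and limited to pre-randomisation values, for example the DASS21 and EPDS scores already collected then.
2. In Variables, withdraw the seven possible mediators from the covariates of the effect model and assign them to a separate analysis, labelled exploratory, that uses both arms. The pre-existing conditions are not mediators; any that are wanted as covariates should be named in advance, not screened.
3. Amend Objective 3 in Table 2, which now confines this work to the intervention group. A mediation analysis needs the contrast between arms, which one arm alone cannot supply.
4. Reconcile the sections that place T1 after allocation with the one that calls it recruitment.

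The cost is revised wording in the Variables, Quantitative analysis and T1 timing text, plus a change to one secondary objective. No new data are needed.
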